## Abstract

**Background:**

Acute sleep deprivation (ASD) can effect mood, attention, memory, alertness and metabolism. Especially, it is often accompanied by cognitive impairment of the brain. Acupuncture is safe and effective for improving cognitive function, but its underlying mechanism is not fully understood. In this study, an event-related potential (ERP) technique will be employed to measure the behavioral, cognitive, and physiological changes produced by electroacupuncture intervention after ASD.

**Methods:**

We will recruit 60 healthy subjects. The participants will be randomly divided into a treatment group, a control group, a sham electroacupuncture group and a blank group, at a 1:1:1:1 ratio. The primary outcome will be determined by the change from baseline to 36 h in the MoCA score. The secondary results include the amplitude and latency of ERP N2 and P3, Go-hit rates, Go-RTs, No-Go-FA rates, the WCST, the Digit Span Subtest of the WAIS, the ESS score and FS-14. The 15 healthy subjects will not receive acupuncture treatment and ASD, but will receive EEG records and cognition functions test at the beginning and end of the experiment. Electroacupuncture intervention will be performed for 30 min once every 12 h, a total of three times. ERP measurements and other tests will be performed after baseline and ASD, and the statistician and outcome evaluator will be blinded to treatment allocation.

**Discussion:**

This study is expected to investigate the effectiveness of electroacupuncture in improving cognition for ASD.

**Trial Registration:**

ChiCTR2200055999.

## Background

Acute sleep deprivation (ASD) is the elimination of sleep for a period of time (at least 24 h) to significantly prolong wakefulness (1). Inadequate sleep and sleep disorders have become an important public health problem. ASD can effect mood, attention, memory, alertness, cognitive performance and metabolism (2, 3). With the increasing pace of life, the incidence of sleep deprivation has increased significantly, which has attracted attention in the military field and many social sectors (such as aviation, navigation, medical treatment, and transportation). The common negative effects of sleep deprivation include feeling too sleepy during the day, accidents from lack of attention, mood changes, and changes in appetite (4). Insufficient sleep increases the risk of human error-related accidents (5). ASD affects cognition in many ways and can negatively impact alertness, learning, memory, and executive function (6–12). Since ASD has serious effects on human cognitive brain function, safety intervention studies on the effects of ASD, such as acupuncture, are increasingly popular in this field (13, 14).

Studies show that administration of caffeine may improve vigilance, alertness, mood and cognitive processes and enhance cognitive processing related to response selection and inhibition (15, 16). Compared with the central nervous system stimulant caffeine, acupuncture is a safe alternative therapy with minimal side effects (17). A Delphi expert consensus survey (18) shows that more than 80% of experts agree that acupuncture can be used to improve cognitive function, which has been underpinned by the results of previous studies (19, 20). Although acupuncture has been studied for a long time, there is still a lack of knowledge of the effects of acupuncture on the human brain. More research is necessary to better understand how brain activity is affected by acupuncture.

Executive function (also called executive control or cognitive control) is fundamental to human cognition (21). It is a top-down mental process needed when one has to concentrate and pay attention, when going on automatic or relying on instinct would be insufficient (22–24). There are three core executive functions: inhibition, working memory (WM), and cognitive flexibility (25, 26). The Go/No-go paradigm has been used to study the executive function (27). Event-related potential (ERP) has often been used to investigate the effects of sleep deprivation on neurocognitive functioning. It is non-invasive and simple to perform, and it does not entail discomfort for participants. Certain components of ERP have been found to reflect specific forms of information processing related to sensory, motor and/or cognitive functions (28). The visual Go/No-go task is often used to study response inhibition (29). There have been several reports supporting the hypothesis that the visual N2 reflects a frontal inhibition mechanism (30, 31), including cognitive control and response inhibition (32, 33). Furthermore, recent studies suggest that P3 may play an important role in the post-response stage, reflecting processes of cognitive processing, such as stimulus identification and evaluation (34, 35) or monitoring of inhibition (36, 37).

This high-quality randomized controlled trial (RCT) was designed *via* a pragmatic trial approach to objectively assess the efficacy of electroacupuncture for brain cognition using ERP. By comparing ERP related to response inhibition tasks before and after ASD, we can understand the effect of ASD on the brain's inhibition control and the effect of electroacupuncture on brain cognition function after ASD.

### Objectives

The aim of this study is to assess the effect of electroacupuncture on brain inhibition control function.

## Methods/Design

### Study Setting

This study is a participant-, statistician-, and assessor-blinded parallel randomized control clinical trial. The study will follow the principles of the Consolidated Standards of Reporting Trials (CONSORT) as well as the Standards for Reporting Interventions in Clinical Trials of Acupuncture (STRICTA) statement for acupuncture. Sixty healthy college students will be randomly assigned to a treatment group, a sham electroacupuncture group and a blank group, at a 1:1:1:1 ratio. The control group will be set to evaluate the efficacy of electroacupuncture. The sham electroacupuncture group be set to rule out placebo effects. The study will be conducted at the Third Affiliated Hospital of Henan University of Traditional Chinese Medicine, Department of Acupuncture, Henan, China, following the Standard Protocol Items: Recommendations for Interventional Trials (SPIRIT). For the participant timeline, see Table 1.

**Table 1 T1:** SPIRIT figure for schedule of enrollment, interventions and assessments.

	**Study Period**						
	**Enrollment**	**Allocation**	**Post-allocation**				**Close-out**
**Timepoint**	** *−1 w* **	**0**	** *Baseline* **	** *12 h* **	** *24 h* **	** *36 h* **	** *48 h* **
**Enrollment**							
Eligibility screen	X						
Informed consent	X						
Baseline assessment	X						
Allocation		X					
**Interventions**							
Treatment group							
Placebo group							
Control group							
Blank group							
**Assessments**							
EHQ	X						
Sleep log	X						
SCL-90	X						
PSQI	X						
MoCA			X			X	
WCST			X			X	
DS			X			X	
ESS			X			X	
FS-14			X			X	
EEG-record			X			X	
Adverse events			X	X	X	X	X

*EHQ, Edinburgh Handedness Questionnaire; SCL-90, Symptom Checklist-90; PSQI, Pittsburgh Sleep Quality Index; MoCA, Montreal Cognitive Assessment; WCST, Wisconsin Card Sorting Test; DS, Digit Span of the Wechsler Adult Intelligence Scale; ESS, Epworth Sleepiness Scale; FS-14, Fatigue Scale-14; EEG, Electroencephalogram*.

### Sample Size

According to the pre-test study, the average MoCA scores in the treatment group, control group, and blank group are 26.70, 25.72, and 27.32, respectively, and the standard deviations are 1.03, 1.59, and 1.37, respectively. Using the sample size calculation method of multi-group mean, the sample size estimation [one-way analysis of variance (ANOVA)] *F*-test] method will use the test level α = 0.05 (bilateral) and test efficiency 1 – β = 0.90. The bilateral test will be used. The total sample size of 45 cases was estimated using PASS 15.0 software.

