## Outcomes

### Primary Outcome

The primary outcome is the MoCA score. The cognitive areas assessed include attention and concentration, executive function, memory, language, visual structure skills, abstract thinking, calculation and orientation, with a total score of 30. The lower the score, the more severe the cognitive impairment.

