**Figure 2 F2:**
[figure not shown]
Trial work plan. The primary outcome measure will be MoCA. The remaining outcome measures will be for secondary outcomes.

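### The primary outcome is the change in MoCA from baseline to 36 h, but the sample size rests on MoCA score levels and their SDs, so the stated 90% power does not belong to the stated endpoint

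*Protocol article*

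**What the plan says.** The Abstract (Methods) gives both metric and time points: "The primary outcome will be determined by the change from baseline to 36 h in the MoCA score". The Primary Outcome section says "The primary outcome is the MoCA score" and describes the scale, "with a total score of 30", without a time point and without saying whether level or change is meant. The Figure 2 legend is equally brief: "The primary outcome measure will be MoCA". Table 1 schedules MoCA at baseline and at 36 h, so either variable can be computed.

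The Sample Size section takes its inputs from a pre-test: "the average MoCA scores in the treatment group, control group, and blank group are 26.70, 25.72, and 27.32, respectively, and the standard deviations are" listed next, as 1.03, 1.59 and 1.37. The time point of those scores is not stated. The section applies a one-way ANOVA F-test at α = 0.05 with power 0.90 and arrives at 45 participants in total.

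The Data Analysis section names repeated-measures ANOVA for the behavioral data and the ERP indices. It does not mention MoCA.

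**The concern.** A score and a within-person change are different variables with different SDs. The calculation uses the between-person spread of scores, whereas the Abstract's endpoint needs the spread of changes. The two are linked by the baseline-to-36-h correlation, which the article does not give. The power claimed for the primary endpoint therefore has no stated basis, and correcting the arithmetic on the same inputs would not supply one.

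The sections that could settle which variable is meant do not do so. On the same data, an F-test on the 36-h score and an F-test on the change can fall on different sides of 0.05. The primary variable should therefore read the same way wherever it is named.

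**Working it through.** **Inputs from the Sample Size section.** Means 26.70, 25.72 and 27.32; SDs 1.03, 1.59 and 1.37; three groups; α = 0.05; total 45, i.e. 15 per group. The trial plans 60 in four arms at 1:1:1:1, which is also 15 per arm.

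**Assumptions, not in the document.** The means are 36-h scores. Expected baselines are equal across arms, as randomisation implies. The SD is the same at both times. r is unknown and is varied.

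**Level or change?** Means near 26 to 27 on a scale with a maximum of 30 can only be levels.

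**Step 1: the plan's own figure.**
- Common SD = √((1.03² + 1.59² + 1.37²)/3) = √1.822 = 1.350.
- Grand mean = 26.58. Sum of squared deviations = 0.12² + 0.86² + 0.74² = 0.0144 + 0.7396 + 0.5476 = 1.3016.
- Noncentrality λ = n × 1.3016 / SD² = 15 × 1.3016 / 1.822 = 10.72.
- The F-test on 2 and 42 df has critical value 3.22 and power 0.814.

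So 45 does not give 90% even for the score. On these inputs 90% needs 19 per group, 57 in total (power 0.904). That is a separate matter. The 81% is the reference for what follows.

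**Step 2: raw change.** SD of change = 1.350 × √(2(1 − r)), with the same expected group differences.

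| r | SD of change | λ | Power, 15 per arm |
|---|---|---|---|
| 0.3 | 1.597 | 7.65 | 0.66 |
| 0.5 | 1.350 | 10.72 | 0.81 |
| 0.7 | 1.046 | 17.86 | 0.96 |

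At r = 0.5 the factor √(2(1 − r)) is 1 and the two powers coincide. Below 0.5 the change has less power than the score, and above it more.

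**Step 3: 36-h score adjusted for baseline.** Residual SD = 1.350 × √(1 − r²). The one degree of freedom spent on the covariate is ignored.

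| r | Residual SD | λ | Power, 15 per arm |
|---|---|---|---|
| 0.3 | 1.288 | 11.78 | 0.85 |
| 0.5 | 1.169 | 14.29 | 0.91 |
| 0.7 | 0.964 | 21.01 | 0.98 |

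Because 1 − r² = (1 − r)(1 + r) is at most 1 and at most 2(1 − r), this SD never exceeds that of either raw metric.

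**Step 4: how often the two raw metrics disagree.** I simulated 100,000 trials of the three-group F-test with 15 per arm. Exactly one of score and change was significant in about 27%, 22% and 19% of trials at r = 0.3, 0.5 and 0.7.

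**Step 5: direction.** For treatment versus control alone (difference 26.70 − 25.72 = 0.98, SD 1.34, 15 per arm), the two estimates had opposite signs in about 6%, 4% and 2% of 100,000 simulated trials at r = 0.2, 0.5 and 0.8. No trial was significant in both directions.

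**The case against.** The strongest defence is that there is only one endpoint. The Abstract gives it in full, Table 1 schedules MoCA at exactly those two times, and the Primary Outcome section and the Figure 2 legend merely name the instrument, as a condensed article may. This stands. A reader might infer that the Outcomes section sets up the raw score as a rival primary endpoint. It does not: it gives neither metric nor time point, so it is under-specified rather than contradictory. The firm mismatch is between the Abstract and the Sample Size section.

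A reader might also infer that the two versions could give opposite primary results. The documents do not support that. Under randomisation both metrics have the same expected difference between arms. They can disagree on significance, but step 5 found no opposite significant results.

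A third tempting inference is an inflated type I error from picking the better metric after seeing the data. For a two-arm comparison that would be about 9% instead of 5%. It presupposes a choice that no section offers, since the Abstract has already named the change.

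Finally, sizing on score SDs need not be optimistic: above r = 0.5 it understates the power on the change, and it is conservative for a baseline-adjusted analysis. This too is correct. The objection leaves untouched that the stated power was computed for a variable other than the stated endpoint, and that nothing in the article allows conversion.

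**Conclusion.** The point holds as a mismatch between the Abstract's endpoint and the Sample Size inputs. With 15 per arm, the three-group test on the change could have power from 66% at r = 0.3 to 96% at r = 0.7, against 81% on the score. The documents do not fix the direction of the effect, so a claim that the trial is underpowered for this reason alone would go too far. The figures rest on the assumptions listed above and on the three-group test the plan itself uses, which leaves out the sham arm. This should be corrected, but it does not undermine the design, because the data needed for either metric are already scheduled.

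**What to change.** Use one definition in the Abstract, Sample Size, Primary Outcome and the Figure 2 legend: MoCA at 36 h, compared between arms with baseline MoCA as covariate. It serves both wordings, because the baseline-adjusted difference in the 36-h score equals the baseline-adjusted difference in change. In Sample Size, say that the inputs are scores and at which time they were taken, and restate the power achieved with 15 per arm for this endpoint over a range of r, for example 0.3 to 0.7.

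If the raw change is preferred, write it with its time points in the Primary Outcome section, replace the inputs with the pre-test mean changes and SDs of change, and restate the power.

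The cost is wording in four places and one recalculation. No participants or assessments are added. The drawback is that the restated power may fall below 90%, as it does at r = 0.3 even with baseline adjustment (85%).

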### Data Analysis

We will use SPSS software version 21.0 (IBM Corp, Armonk, New York, US) to perform data analysis. Demographic and baseline data will be analyzed with standard descriptive statistics. Data will be presented as the mean ± standard deviation (SD). A repeated measure ANOVA is employed to analyze the electroacupuncture effects and the time effects on the behavioral data. The repeated measure ANOVA is also used for the analysis of ERP indices. ANOVAs are performed on the N2 and P3 components of the scalp electrodes in the Go/No-Go task. The accepted level of significance for all analyses will be *P* < 0.05.

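### The 90% power belongs to a three-group F-test that includes the rested blank arm and mostly measures sleep loss; it is not power for the electroacupuncture effect

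*Protocol article*

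**What the plan says.** Under Sample Size, the protocol article reports pre-test results for three of the four arms: "the average MoCA scores in the treatment group, control group, and blank group are 26.70, 25.72, and 27.32, respectively". For spread, listed in the same arm order, it says that "the standard deviations are 1.03, 1.59, and 1.37, respectively". The calculation is described as "Using the sample size calculation method of multi-group mean", a one-way ANOVA F-test at a 0.05 level with "test efficiency 1 – β = 0.90". It arrives at 45 participants, which is 15 per arm over three arms. The Abstract plans 60 participants in four arms at 1:1:1:1, again 15 per arm.

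The arm descriptions show what the three means represent. The treatment arm is sleep deprived and receives electroacupuncture. The control arm is sleep deprived and untreated. The blank arm is neither deprived nor treated.

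Under Objectives, the aim is the effect of electroacupuncture. Under Study Setting, "The control group will be set to evaluate the efficacy of electroacupuncture", and the sham arm is there to rule out placebo effects. The Abstract defines the primary outcome as the change in MoCA from baseline to 36 h.

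Under Data Analysis, "A repeated measure ANOVA is employed to analyze the electroacupuncture effects and the time effects on the behavioral data", and the same method is used for the ERP indices. Secondary Outcomes defines the behavioural variables as Go/No-Go reaction time, hits and false alarms. No test is named for MoCA.

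**The concern.** The only test tied to the primary outcome is an omnibus comparison that includes a rested arm. An omnibus F-test responds to any difference among the means. Here the largest difference is between people who slept and people who did not, which is not what the trial sets out to learn. The assumed electroacupuncture mean lies between the other two, so a real benefit pulls the three means closer together and lowers the power of the test.

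What is at stake is the meaning of the stated 90%. A reader will take it as the chance of detecting the electroacupuncture effect. No comparison of electroacupuncture with control or with sham is sized anywhere in the article, and the most relevant one has much lower power. This is separate from whether 45 is the right number for the F-test, and from the absence of the sham arm from the calculation. A correctly computed 90% would still answer a different question.

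**Working it through.** **Inputs (Sample Size section).** Means: treatment T = 26.70, control C = 25.72, blank B = 27.32. SDs 1.03, 1.59, 1.37. Two-sided alpha 0.05, 15 per arm. Common SD by root mean square: √[(1.03² + 1.59² + 1.37²)/3] = √1.822 = 1.35.

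**1. The plan's own figure.** The noncentrality is λ = n·Σ(mean − grand mean)²/SD². The grand mean is 26.58, and the squared deviations are 0.0144 + 0.7396 + 0.5476 = 1.3016. At n = 15, λ = 15 × 1.3016/1.822 = 10.7, with 2 and 42 degrees of freedom. Power is 81%, not 90%. On this SD, 90% needs 19 per arm (57 in three arms). The shortfall is a separate matter and is given only so that the later figures have a base.

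**2. Where the signal comes from.**
- Control versus blank: (27.32 − 25.72)²/2 = 1.60²/2 = 1.28.
- Treatment versus the average of the other two (26.52): 0.18² × 2/3 = 0.0216.
- Together 1.3016. The share of control versus blank is 1.28/1.3016 = 98%.

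**3. The same test if electroacupuncture does nothing.** Set T = C = 25.72 and leave B unchanged. The sum of squares becomes 1.707 and λ = 15 × 1.707/1.822 = 14.05. Power is 91%.

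| Common SD | Works as assumed | Does nothing |
|---|---|---|
| 1.03 (smallest) | 97% | 99% |
| 1.33 (mean) | 83% | 92% |
| 1.35 (root mean square) | 81% | 91% |
| 1.37 (blank arm) | 80% | 90% |
| 1.59 (largest) | 67% | 79% |

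Simulation with the three unequal SDs gives 78% as assumed. With no effect it gives 91% (treatment SD 1.03) or 84% (treatment SD 1.59).

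**4. Four arms of 15.** The article gives no sham mean, so this step rests on assumptions. Degrees of freedom are 3 and 56, SD 1.35.
- No effect of either needling: sum of squares 1.92, λ = 15.8, power 91%.
- Effect as assumed, sham = control: sum of squares 1.856, λ = 15.3, power 90%.
- Effect as assumed, sham midway between control and treatment: 80%.
- Effect as assumed, sham = treatment: 76%.

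**5. The electroacupuncture contrast.** T − C = 0.98, standard error 1.35 × √(2/15) = 0.493, noncentrality 0.98/0.493 = 1.99. The two-sided t-test has 48% power on 28 degrees of freedom and 49% on 42 (error taken from three deprived arms). The SD of these two arms alone, √[(1.03² + 1.59²)/2] = 1.34, also gives 49%. The 95% CI half-width is 2.02 × 0.493 = 1.0 point, as large as the assumed effect.

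**6. The stated endpoint.** Assume equal SDs at both times and a baseline correlation r, which the article does not give. A change score has SD 1.35·√[2(1 − r)]; baseline adjustment gives 1.35·√(1 − r²).

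| r | Change score | Baseline-adjusted |
|---|---|---|
| 0.3 | 37% | 52% |
| 0.5 | 48% | 60% |
| 0.7 | 70% | 77% |

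**7. Electroacupuncture versus sham.** If sham keeps half the benefit (an assumption), the difference is 0.49 points and power is about 16%.

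**The case against.** The strongest reply is that a sizing test is not an analysis plan. A reader might infer that the omnibus F-test is the primary analysis, and that the trial could be declared positive for electroacupuncture merely because lost sleep lowers the MoCA. The article does not support that. Data Analysis names no MoCA test, its repeated-measures ANOVA is assigned to behavioural and ERP data, and follow-up contrasts are commonly left to a fuller document. The Discussion lists the interventions to be compared as electroacupuncture, sham and no electroacupuncture, measured at baseline and after deprivation. That reads most naturally as the deprived arms only, although it concerns the Go/No-Go task and does not settle MoCA.

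A reader might also infer that the trial as designed is more likely to be significant if electroacupuncture fails. That ordering belongs to the three-group calculation. With four arms and sham equal to control it is close to a tie, and simulation with unequal SDs can reverse it slightly (86% with the effect, 84% without, when the treatment SD without an effect is set to 1.59). What remains is that such a test barely distinguishes the two situations.

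Finally, 49% is for a single-time-point score, whereas the endpoint is a change, so the ranges in step 6 are the fairer statement. The Discussion does concede that the sample is small, but that does not tell the reader which question the 90% refers to.

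**Conclusion.** Wrong as written, within limits. The stated 90% is power for a three-group comparison dominated by sleep deprivation (98% of the signal on the protocol's own means). It is not power for the electroacupuncture effect named in Objectives and Study Setting. In that calculation power is about 81% with the assumed benefit and about 91% without it, and this order holds for every common SD tried.

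Treatment versus control has about 49% power on a single-time-point score. The ranges for the change-from-baseline endpoint, 37-70% for change scores and 52-77% with baseline adjustment, rest on an assumed correlation of 0.3-0.7 and equal SDs at both times. All of them fall short of 90%. Doing nothing is taken to mean that the treatment mean equals the control mean with the blank mean unchanged. The four-arm and sham figures depend on sham means that the article does not supply. The conclusion concerns the basis for the sample size and does not establish that the primary analysis will be an omnibus test.

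**What to change.** - Name the primary MoCA contrast among the sleep-deprived arms. Study Setting gives the untreated control arm the efficacy role; whether control or sham comes first is the sponsor's choice.
- Keep blank versus control as a separate check that deprivation lowered the score, and say that the omnibus F-test is not evidence on electroacupuncture.
- In Sample Size, replace the 90% with the power of the named contrast at 15 per arm, or with its expected 95% CI half-width (about 1.0 point unadjusted). State whether the figure is for a single-time-point, change or baseline-adjusted score, and the correlation assumed.
- If electroacupuncture versus sham is chosen, state the assumed sham mean. The 0.98-point difference is treatment versus control and cannot be carried over.

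The cost is wording and a less favourable stated power. These changes require no extra participants. Holding to 90% for 0.98 points on an unadjusted single-time-point score would be a different decision, at about 41 per arm (t-test, SD 1.34).

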## Control Group

Participants in the control group will receive only 36-h ASD but will not receive electroacupuncture treatment.

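### The stated 90% power belongs to a three-group F-test that includes the non-sleep-deprived blank group, so it mainly measures the effect of sleep loss and not of electroacupuncture

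*Protocol article*

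**What the plan says.** **Sizing.** The Sample Size section takes its inputs from a pre-test study: "the average MoCA scores in the treatment group, control group, and blank group are 26.70, 25.72, and 27.32", and "the standard deviations are 1.03, 1.59, and 1.37, respectively". It gives the method as "Using the sample size calculation method of multi-group mean, the sample size estimation [one-way analysis of variance (ANOVA" F-test), applies it at "test level α = 0.05 (bilateral) and test efficiency 1 – β = 0.90" and arrives at 45 in total, which is 15 in each of three groups. No mean or SD is given for the sham arm. The trial enrols 60 in four equal arms, so 15 per arm.

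**Arms.** The Abstract and the Blank Group section state that the blank group has no sleep deprivation and no acupuncture. For the control group: "Participants in the control group will receive only 36-h ASD but will not receive electroacupuncture treatment". On roles, Study Setting says "The control group will be set to evaluate the efficacy of electroacupuncture", and its next sentence gives the sham arm the task of excluding placebo effects.

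**Outcome and analysis.** The Abstract defines the primary outcome as change in MoCA from baseline to 36 h. Data Analysis plans repeated-measures ANOVA for behavioural and ERP data and names no test for MoCA. It adds "The accepted level of significance for all analyses will be" P < 0.05.

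**Blinding.** Study Setting states "This study is a participant-, statistician-, and assessor-blinded parallel randomized control clinical trial". The Blinding section lists only outcome assessors and data analysts.

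**The concern.** The stated objective concerns electroacupuncture. The only between-group test that the article attaches to MoCA includes a group that was allowed to sleep. A test of equality across treatment, control and blank can be significant for a reason unrelated to needling: the blank group slept and the others did not. The Discussion already treats impairment after sleep deprivation as evident.

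Two things are at stake. First, the 90% power is stated for a hypothesis other than the one the trial was set up to examine, so a reader will think the electroacupuncture comparison better supported than it is. Second, if the sizing test were carried over to the primary analysis, a significant result could be reported as an electroacupuncture effect when it shows only sleep loss.

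**Working it through.** **Inputs** (Sample Size section): means 26.70 (treatment), 25.72 (control), 27.32 (blank); SDs 1.03, 1.59, 1.37; n = 15 per arm. Common variance = (1.03² + 1.59² + 1.37²)/3 = 5.4659/3 = 1.822, so SD = 1.35.

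**Formula.** One-way ANOVA power comes from the noncentral F distribution with λ = n·Σ(μᵢ − μ̄)²/SD².

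**1. The plan's own figure.** The grand mean is 26.58. Σ(μᵢ − μ̄)² = 0.12² + 0.86² + 0.74² = 1.3016. With n = 15, λ = 15 × 1.3016/1.822 = 10.7, and power on F(2, 42) is **0.81**. Reaching 0.90 takes 19 per group, 57 in total, so 45 at 90% does not reproduce with this SD; a common SD of about 1.20 would be needed. That is a separate point. It matters here only because 0.81 is the benchmark for step 3.

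**2. What drives the test.** Split the 1.3016 into two orthogonal parts:
- treatment versus control: 0.98²/2 = 0.480, or 37%;
- blank versus the mean of the two deprived arms (26.21): 1.11² × 2/3 = 0.821, or 63%.

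**3. Rejection rate if electroacupuncture does nothing.** Set treatment equal to control at 25.72 and leave blank at 27.32.
- Three groups: Σ = 1.60² × 2/3 = 1.707, λ = 14.05, rejection probability **0.909**.
- Four groups, sham also at 25.72: Σ = 1.60² × 3/4 = 1.92, λ = 15.8, rejection probability **0.912**.

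The test therefore rejects more often when electroacupuncture fails (0.91) than when it works as planned (0.81). With the blank group left out, the rate under no electroacupuncture effect is 0.05.

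**4. Sensitivity of the 0.91.**
- All deprived arms given the control SD of 1.59, blank 1.37: 0.84 by simulation.
- Change scores: the baseline-to-36 h correlation ρ is not given. Assume equal SDs of 1.35 at both times and no baseline differences, so that SD of change = 1.35·√(2(1 − ρ)). The four-group rate is then 0.61 (ρ = 0), 0.78 (0.3), 0.91 (0.5) and 0.99 (0.7).
- Smaller sleep-loss effect, three groups, SD 1.35: with both deprived arms at 26.21 the rate is 0.61; with both at 26.70 it is 0.22.

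Every one of these is well above 0.05.

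**5. The contrast of interest.** Treatment versus control: difference 26.70 − 25.72 = 0.98; SD = √((1.03² + 1.59²)/2) = 1.34; noncentrality 0.98/(1.34·√(2/15)) = 2.00 on 28 df. Two-sided power at 0.05 is **0.49**. On change scores, with the SD multiplied by √(2(1 − ρ)), it is 0.28 (ρ = 0), 0.37 (0.3), 0.49 (0.5) and 0.70 (0.7). As a measure of the gap, 90% power on the stated inputs would need about 41 per arm. Power against sham cannot be computed from the article. If sham captured half the effect (an assumption; difference 0.49), it would be 0.16.

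**The case against.** The strongest reply is that the F-test is fixed for sizing only. That is correct. Data Analysis names no MoCA test, and the Discussion lists the intervention levels as electroacupuncture, sham and no electroacupuncture, without the blank group, though for the Go/No-Go task. A reader might infer that the omnibus F-test is the planned primary analysis; the article does not say so. An analysis plan that is not shown may name a contrast. It would not change the fact that the sample size and its 90% were computed for another hypothesis.

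It is also fair to say that 91% is not a fixed property of the trial. It rests on a common SD, on raw scores and on the pre-test gap between blank and control. The range in the working replaces a single figure, and the conclusion survives across it.

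Three stronger readings are not supported:
- **Unadjusted pairwise tests with about 20% family-wise error.** No pairwise tests are stated, and a nominal 0.05 is compatible with adjusted p-values. In simulation, six pairwise t-tests run only after a significant F-test give about 5% when no group differs, and about 12% among the three deprived arms when only blank differs.
- **Electroacupuncture versus control as an open-label comparison.** Participants know whether they are needled, but assessors and the statistician are blinded throughout.
- **Sham as the only legitimate first contrast.** Study Setting gives both control and sham a role, so the order is open to choice.

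**Conclusion.** The point holds for the sizing. The stated power attaches to a test that includes a group differing from the others by sleep, and that difference dominates the result. On the article's inputs with 15 per arm and SD 1.35, the test rejects about 91% of the time with no electroacupuncture effect and 81% under the planned means; electroacupuncture versus control has about 49% power. These figures assume raw scores and the pre-test means and SDs. Whether the blank group would enter the final MoCA test is not stated, so the consequence for the trial's conclusion is conditional: if the same F-test were used, its significance would not be evidence for electroacupuncture.

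The participant-blinded claim is too broad. It cannot cover the control and blank arms, whose participants receive no needling. It can apply only to electroacupuncture versus sham.

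**What to change.** 1. Leave the blank group out of the confirmatory MoCA test. Use blank versus control only as a check that sleep deprivation impaired MoCA.
2. Name the electroacupuncture contrast or contrasts on change in MoCA to 36 h among the sleep-deprived arms: versus sham and versus control, in a fixed order or Holm-adjusted. The order is the sponsor's choice.
3. Replace the 90% statement with the power of the named contrast: about 49% versus control on the stated inputs. For sham, state the assumed mean and show a range. State the assumed baseline correlation, since the outcome is a change score.
4. In Study Setting, limit the participant-blinded claim to electroacupuncture versus sham, and note that all comparisons remain assessor-blinded.

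**Cost.** A revision of the text and a recalculated power statement. No added enrolment is proposed, so the trial would openly carry much lower power for its own question than the article now suggests.
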